### Proposed sample size

The sample size is based on testing group differences in the primary outcome, excess time to ACHD care, with a two-sided log-rank test. A sample size of 60 patients per group (120 total) will allow detection of a difference between 90 and 70 %, the proportions that have attended their first ACHD clinic appointment by the end of the observation period in the intervention and usual care groups, respectively, with 80 + % power (Type I Error Probability [α] = 0.05), accounting for the “design effect” due to the cluster randomization of the trial. The proportion of 70 % in the usual care group is conservative, as published SickKids data suggests it may be as low as 50 % [8]. If the proportion of usual care participants attending the ACHD clinic is <70 %, the study power will be even higher. The difference between 90 and 70 % is the minimum clinically important difference, as a proportion <90 % attending ACHD care is unacceptably low [15]. Given that the most common reason for a lapse in care prior to first ACHD visit is a belief that cardiac follow-up is not required [9], a misconception that the intervention will address, we believe that a 90 % ACHD clinic attendance in the intervention group is achievable.

### Quantitative data analysis

Intention-to-treat analysis will be used and all statistical tests will be two-sided. Baseline characteristics of the control (usual care) and intervention groups will be summarized using descriptive statistics (e.g., means, medians, standard deviations, frequencies, proportions). Kaplan-Meier plots will display excess time to first ACHD appointment by treatment group. Log-rank tests with a cluster-level bootstrap will test the difference in the excess time distribution between the intervention and control groups. The cluster sizes are likely to be 3–4. All statistical analyses will account for the cluster randomization. Participants who have not attended the ACHD clinic by the end of the study period (i.e., are censored) will still contribute to the primary outcome, as survival analysis is designed to accommodate censored data. We will assess differences in mean scores of each secondary outcome at baseline, 1, 6, 12, and 18 months, where applicable, by treatment group using general linear mixed models [24] that take both the cluster randomization and longitudinal nature of the data into account. Additional analyses will be stratified by a) study site (Edmonton versus Toronto) and b) attended first ACHD appointment (yes/no).

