### Usual care

No transition program is formally in place at the Stollery site. Families receive written information about their child’s CHD, suggested timelines for increasing teens’ self-management of his/her CHD, and at the last pediatric visit a “graduation” package with information about the ACHD program is provided. At SickKids, usual care is similar. However, to account for potential differences in usual care, randomization will be stratified by site. With multiple pediatric cardiologists and clinic nurses at each site, clinician-led education is likely variable and constrained by limited clinic time. At both sites, pertinent medical records are sent to ACHD providers at the time of transfer. Both ACHD clinics send a welcome letter to patients indicating approximately when their first ACHD appointment will be. A second letter is sent one month prior to the first ACHD appointment with the date and time. Patients who do not attend are contacted by telephone to reschedule. All components of usual care will be tracked by the project coordinator at each site, and any change in usual care during the study will be documented.

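### Randomisation is stratified by site, but the primary clustered log-rank test names no site strata, which costs power if attendance differs between the two sites

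*Protocol article*

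**What the plan says.** In the Protocol article, *Usual care* states that "to account for potential differences in usual care, randomization will be stratified by site". *Group allocation* makes the clinic week the unit of randomisation, with at most four patients per week.

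*Quantitative data analysis* gives the primary analysis: "Log-rank tests with a cluster-level bootstrap will test the difference in the excess time distribution between the intervention and control groups". It adds that "All statistical analyses will account for the cluster randomization". Site is mentioned once in that section: "Additional analyses will be stratified by a) study site (Edmonton versus Toronto) and b) attended first ACHD appointment (yes/no".

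*Proposed sample size* is built on "excess time to ACHD care, with a two-sided log-rank test" and claims its result "with 80 + % power (Type I Error Probability [α] = 0.05), accounting for the “design effect” due to the cluster randomization of the trial". No intracluster correlation and no site-specific attendance rates are given.

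**The concern.** The design and the primary test treat site differently. Stratifying the randomisation by site aims to balance the arms within each site, so a site difference in attendance largely cancels from the treatment comparison. A test that pools the sites still leaves that difference in its variance. The comparison is then more precise than the test assumes, so the type I error falls below 5% and power is lost.

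Clustering makes this worse. All patients in one week come from one site, so a site difference looks like variation between weeks. If the bootstrap resamples weeks without regard to site, it brings back the variation that the design removed. At stake is some of the power of a 120-patient trial.

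**Working it through.** **1. The plan's own power.** Inputs from *Proposed sample size*: 60 per group, 90% versus 70% attended, two-sided alpha 0.05.

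- Hazard ratio = ln(0.10)/ln(0.30) = 1.912.
- Events = 0.90 × 60 + 0.70 × 60 = 54 + 42 = 96.
- Schoenfeld power = Φ(√(96/4) × ln 1.912 − 1.96) = 88.8%.
- Dividing events by the design effect 1 + (m − 1) × ICC with m = 4: ICC 0.05 gives a design effect of 1.15 and power 84.2%; ICC 0.10 gives 1.30 and 79.6%.

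The stated power of 80% or more therefore reproduces for a design effect up to 1.28. The ICC is not stated.

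**2. Why pooling costs power.** Write the log-rank score as U = Σ R_c, where R_c is the sum of patient score terms in week c. The cluster-robust variance is (C/(C − 1)) × Σ R_c², with C the number of weeks. At the site with faster attendance, pooling shifts R_c by roughly +δ in intervention weeks and −δ in usual care weeks; at the slower site the signs reverse. With equal numbers of weeks per arm within site, the shifts cancel in U, but each adds about δ² to the variance. Computing the score within site removes δ from both.

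**3. Size of the loss, cluster-robust variance.** Assumptions: 120 patients in 30 weeks of 4, sites of 16 and 14 weeks, weeks balanced by arm within site, exponential times, treatment hazard ratio 1.912 or 1, and no extra week effect. There were 6,000 runs per setting. Site hazard ratio = ln(1 − pA)/ln(1 − pB).

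| Control attendance, site A/B | Site HR | Type I error, pooled / stratified | Power, pooled / stratified | Points lost |
|---|---|---|---|---|
| 70/70 | 1.00 | 5.2% / 5.8% | 87.1% / 87.6% | 0.5 |
| 75/65 | 1.32 | 4.2% / 5.1% | 85.8% / 88.0% | 2.2 |
| 80/60 | 1.76 | 3.2% / 5.8% | 80.3% / 87.7% | 7.4 |
| 85/55 | 2.38 | 1.6% / 5.9% | 68.0% / 88.1% | 20.1 |
| 90/50 | 3.32 | 0.5% / 5.8% | 50.0% / 87.4% | 37.4 |

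The last two rows show the range; they are not expected values. With gamma week frailty of variance 0.1, the 80/60 row becomes 67.3% pooled and 75.6% stratified.

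**4. Separate check with a permutation reference.** This used 32 week-clusters balanced within site and 700 runs per setting (simulation error about ±1.96 × √(0.85 × 0.15/700) = ±2.6 points). Power, pooled versus stratified:

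- no site effect: 86% versus 85%;
- site HR 1.5 (control attendance about 77/63): 83% versus 86%;
- site HR 2 (about 82/57): 74% versus 85%, with type I error 1.9% versus 4.4%.

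**5. Weeks not balanced within site.** With simple randomisation of weeks at 80/60 (4,000 runs), the pooled clustered test keeps 5.0% type I error. Its power is 74.8%, against 83.6% stratified. With equal sites the order reverses slightly: 86.1% pooled, 84.6% stratified.

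**6. An actual cluster bootstrap.** This used 30 weeks of 4, 400 runs and 150 resamples, with z referred to 1.96. It compares pooled resampling within arm with a stratified statistic resampled within site and arm.

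| Control attendance | Type I error, pooled / stratified | Power, pooled / stratified |
|---|---|---|
| 70/70 | 7.2% / 8.2% | 89.5% / 91.8% |
| 80/60 | 5.0% / 8.0% | 84.5% / 91.2% |
| 90/50 | 0.8% / 9.5% | 59.0% / 90.2% |

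A second bootstrap check (32 weeks of 3 to 4 patients, 800 runs, 200 resamples) rejected 7 to 10% of the time under the null when resampling within site and arm. Pooled resampling gave 6 to 8% with no site effect, 5 to 6% at site HR 1.5, 4 to 5% at HR 2 and 1 to 3% at HR 3. Part of the stratified bootstrap's apparent power gain is therefore inflated size.

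**The case against.** **Site may not matter.** *Usual care* describes care at SickKids as similar to that at Stollery and speaks only of potential differences. Both adult clinics send the same two letters and telephone patients who miss a visit. A reader might infer that site is strongly prognostic, but the documents do not support this. They cite published SickKids data suggesting attendance as low as 50%, with no Edmonton figure beside it. This objection stands: the size of the loss is conditional.

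**The analysis plan may settle it.** The article is condensed, the resampling scheme is not described, and accounting for the cluster randomisation could be read to include its strata. This stands in part, since nothing forbids site strata. However, the article does more than stay silent: it names the primary test and places site among the additional analyses.

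**The pooled bootstrap is close to nominal at moderate site differences.** This is true (step 6), but only because a simple bootstrap's liberality offsets the conservatism from ignoring site. It argues for a better reference distribution, and it rules out simply moving the plain bootstrap inside site and arm.

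**Ordinary log-rank simulations show a smaller loss.** At 80/60 they give 86.7% pooled and 88.4% stratified. That test ignores weeks, so it is not the planned one.

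**Conclusion.** The point holds as a mismatch between design and primary analysis with a conditional cost. If attendance differs between sites and weeks are balanced by arm within site, a pooled clustered test is conservative. It loses about 3 points of power at a site hazard ratio of 1.5, and 7 to 11 points at control attendance of about 80/60 to 82/57. If weeks are not balanced within site (*Group allocation* describes no blocking), type I error stays near 5% but power is still lost. If the sites do not differ, stratifying changes power by between a gain of 0.5 and a loss of 1.5 points (steps 3 to 5).

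The site rates, the near-equal split and the week frailty are assumptions. Two stronger readings are not supported:

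- **False positives.** Ignoring site lowers the type I error of a clustered test or leaves it unchanged.
- **A margin already spent.** A reader might infer that the design effect has used up the room above 80%. No ICC is stated, and power is 84.2% at ICC 0.05 but 79.6% at 0.10, so the remaining room is unknown.

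**What to change.** - State that the primary test is a log-rank test stratified by site that accounts for week clusters within site.
- Specify a reference distribution that holds its level with about 30 clusters. Options are re-randomising weeks within site according to the actual allocation scheme, a small-sample-corrected bootstrap, or a small-sample-corrected robust variance. Do not use a simple bootstrap within site and arm referred to 1.96. Confirm the chosen method's type I error by simulation before analysis.
- Add site as a fixed effect in the secondary mixed models.
- Keep the by-site results as descriptive.

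The cost is a few sentences in the analysis plan and a short simulation. No extra patients or data are needed, because site is already recorded. If the unseen analysis plan already stratifies the primary test by site, only the calibration of the reference distribution remains to be checked.

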### Study setting and participants

The study will be conducted at The Hospital for Sick Children (“SickKids”, Toronto, Canada) and the Stollery Children’s Hospital (Edmonton, Canada). These are the largest pediatric cardiology programs in Canada and offer the full range of cardiology and cardiac surgical subspecialty services. We will include 16–17 year olds with moderate or complex CHD (as previously defined) [20] who have not yet been transferred to adult care. Exclusion criteria will be (i) less than a Grade 6 level of reading and comprehension, based on parent report, and (ii) heart transplantation.

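### The primary log-rank test leaves out site, the factor that stratifies randomisation, and CHD complexity: a nearly free efficiency gain, not an error

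*Protocol article*

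**What the plan says.** In the protocol article, Quantitative data analysis gives the primary comparison: "Log-rank tests with a cluster-level bootstrap will test the difference in the excess time distribution between the intervention and control groups". It names no stratum and no baseline covariate. The same paragraph plans further analyses stratified by site and by whether the first adult appointment took place, but labels them additional. Complexity is not mentioned there.

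Proposed sample size rests on the same comparison, "with a two-sided log-rank test": "A sample size of 60 patients per group (120 total") to detect a "difference between 90 and 70 %, the proportions that have attended their first ACHD clinic appointment by the end of the observation period", with "80 + % power (Type I Error Probability [α] = 0.05") after allowing for the design effect "due to the cluster randomization of the trial". No intracluster correlation is given.

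Two baseline facts bear on this. Under Usual care, "randomization will be stratified by site", and the reason given is possible differences in usual care between the hospitals. Under Study setting and participants, "We will include 16–17 year olds with moderate or complex CHD", so each participant's complexity class can be established at entry. Group allocation makes the clinic week the unit of randomisation. Complexity is not a stratification factor.

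**The concern.** When randomisation is stratified, the analysis normally carries the same stratum. If site affects time to adult care, stratified allocation removes most of the between-site variation from the treatment comparison. A test that ignores site puts that variation back into its reference distribution, and so does a bootstrap that draws weeks without regard to site. The test then tends to be conservative and gives up precision that the design has already secured.

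Complexity is a weaker second candidate. It is available for everyone, treatment cannot affect it, and randomisation does not balance it. With 120 participants in weeks of 3 to 4, there are about 120/4 = 30 to 120/3 = 40 clusters, or 15 to 20 per arm. A visible chance imbalance is possible. If one appeared, an adjustment decided afterwards would be open to question; one written down beforehand would not.

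**Working it through.** **1. The plan's own power.** Inputs from Proposed sample size: 60 per group, 90% versus 70% attending, two-sided alpha 0.05.

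- Implied hazard ratio under proportional hazards: ln(0.1)/ln(0.3) = 1.91, so the log hazard ratio is 0.648.
- Expected events: 60 × 0.9 + 60 × 0.7 = 54 + 42 = 96.
- Schoenfeld power before clustering: Φ(√(96/4) × 0.648 − 1.96) = 88.8%. Freedman's formula gives 86.6%.
- Design effect: 1 + (m − 1) × ICC, with events divided by it. At m = 3.5, power is 85.0% at ICC 0.05 and 81.1% at ICC 0.10.
- Events needed for 80%: 75 by Schoenfeld. The largest tolerable design effect is 96/75 = 1.28, so the ICC may reach 0.28/2.5 = 0.11 at m = 3.5 (0.14 at m = 3, 0.09 at m = 4). Freedman's formula needs 80 events and allows an ICC of 0.07 to 0.10.

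The claim of at least 80% therefore reproduces without any adjustment, for ICC values up to roughly 0.1.

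**2. Site.** The article gives neither the split of participants between hospitals nor the size of any site difference. No power gain can be computed. The argument is one of consistency between design and analysis.

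**3. Complexity.** The share with complex CHD and its effect on attendance are not given, so both are assumed. The simulation used 3,000 trials per setting, 60 per arm, exponential times, no clustering, and marginal attendance held at 90% and 70%. The Monte Carlo standard error of one power figure is about √(0.9 × 0.1/3000) = 0.5 points.

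| Share complex | Hazard ratio of complexity | Unadjusted log-rank | Stratified log-rank | Adjusted Cox |
|---|---|---|---|---|
| 50% | 1.0 | 88.5% | 87.9% | 88.0% |
| 50% | 1.5 | 89.0% | 90.3% | 90.5% |
| 50% | 2 | 90.5% | 93.6% | 93.5% |
| 50% | 3 | 91.2% | 97.6% | 97.6% |
| 30% | 1.0 | 87.9% | 87.3% | 87.6% |
| 30% | 1.5 | 90.4% | 91.1% | 91.3% |
| 30% | 2 | 89.9% | 92.3% | 92.7% |
| 30% | 3 | 89.6% | 94.4% | 94.8% |

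Type I error was 4.6% to 5.5% for all three tests.

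**4. Chance imbalance in complexity.** With a 50% share, the SD of the between-arm difference is √(2 × 0.25/60) = 9.1 points. It rises to 10.2 points if complexity itself has an ICC of 0.10 within weeks (design effect 1.25). At complexity hazard ratio 2, a one-SD gap moves the log hazard ratio by 0.091 × ln 2 = 0.063, about 10% of 0.648. A 20-point gap moves it by 0.20 × ln 2 = 0.139, or 21%. Such a gap is 0.20/0.091 = 2.2 SD, two-sided probability about 2.8%, or 1 in 35. It nears 1 in 20 only at an SD of about 10 points.

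**The case against.** The case for leaving the plan alone is substantial, and most of it stands.

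- The planned test is coherent. It matches the test used for the sample size, holds its level, and delivers the stated power. Chance imbalance is already covered by its error rate.
- Nothing in the article links complexity to excess time. The Outcome measures section subtracts each patient's recommended interval, so any effect of complexity on that interval is removed before testing. A reader might infer that complexity must be prognostic through follow-up frequency; the endpoint's definition rules that route out.
- Other factors compete. Proposed sample size names the belief that follow-up is unnecessary as the commonest reason for a lapse. That points as readily to baseline knowledge (the MyHeart scale) as to anatomy.
- Usual care describes the two hospitals' practice as similar, so the site effect may be small.
- An analysis plan that is not shown could add strata.

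The last argument carries less weight than the others. The article does not simply leave strata open: it states the primary test and places site among the additional analyses, so an analysis plan would have to change or supplement that choice.

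A reader might also infer that site is confounded with treatment, because Group allocation allows the ratio of intervention to usual care weeks to change midway. That would need the change to differ by site, which the article does not say.

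**Conclusion.** The point holds as an inexpensive efficiency improvement, led by site. The authors stratify randomisation by site for a reason that they state, and the stated primary test does not carry it. Complexity is a secondary addition whose value depends on an assumption: about 0 points of power if it is not prognostic, about 1 at a hazard ratio of 1.5, 2 to 3 at 2, and 5 to 6 only at 3, for which the article gives no support. If complexity has no prognostic value, the apparent loss is 0.6 points or less, about one Monte Carlo standard error.

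A reader might infer that the trial is underpowered or its primary test invalid because baseline factors are omitted. The documents do not support either reading: the size is right, and at least 80% power reproduces up to an ICC of about 0.11 at 3.5 participants per week.

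The simulated figures ignore clustering, the bootstrap, and the cluster of zero values that arises because early attenders are assigned zero excess time. They indicate the order of the gain, not its exact size under the planned analysis.

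**What to change.** Before outcome data are seen:

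1. Make the primary test a log-rank stratified by site, keeping the cluster-level bootstrap but resampling weeks within site.
2. Include CHD complexity (moderate or complex) as one pre-specified factor in a fixed form, either a second stratum or a Cox covariate. Choose the form in advance and do not switch if strata turn out thin. The two forms gave nearly the same power above (93.6% and 93.5% at hazard ratio 2 with a 50% share).
3. Report a hazard ratio with 95% CI from a site-stratified Cox model with week-level clustering, handling complexity in the same form.
4. Keep the unadjusted log-rank as a supportive analysis.

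The cost is a few sentences of analysis text and no new data. Two side effects should be accepted knowingly. Resampling within site leaves fewer weeks per cell: 30 to 40 weeks over four site-by-arm cells is about 8 to 10 each, if the sites recruit equally. An adjusted hazard ratio is conditional, so it need not equal the marginal 1.91 implied by the sample size; in the simulation with complexity hazard ratio 2 and a 50% share it was 2.05.

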### Group allocation

Participants will be randomized by clusters defined by week of attendance in the pediatric cardiology clinic. As week (not study participant) is the unit of randomization, this is a cluster randomization design. This method of randomization: 1) prevents two adolescents in the same waiting room being allocated to different groups and 2) facilitates scheduling of study RNs, who will be available at short notice to provide the intervention during intervention weeks. Cardiologists will not be informed of group assignment, preventing potential bias by cardiologist co-intervention. We anticipate enrollment of 3–4 patients per week, i.e., cluster size will be ≤ 4. To determine which weeks are “intervention weeks” vs. “usual care weeks”, a biostatistician will prepare a randomization sequence.

A 1:1 ratio of intervention: usual care weeks will be used until midway through enrollment, when there will be a re-evaluation. If there is an imbalance, then there will be an adjustment of the ratio of intervention to usual care weeks.

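### With about 30–40 randomised clinic weeks, the planned cluster-bootstrap log-rank test does not reliably hold the 5% level unless it resamples under the null; re-randomising the week labels within site held about 5% in simulation

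*Protocol article*

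**What the plan says.** All of the following is in the protocol article.

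- **Unit of randomisation** (Group allocation): "As week (not study participant) is the unit of randomization, this is a cluster randomization design". Clusters are expected to hold at most 4 patients. A biostatistician prepares the sequence of weeks. The ratio is 1:1 until midway, when it may be adjusted for imbalance.
- **Strata** (Usual care): randomisation is stratified by site.
- **Level and size** (Proposed sample size): the calculation concerns "excess time to ACHD care, with a two-sided log-rank test", with 60 patients per group and a claimed "80 + % power (Type I Error Probability [α] = 0.05" after an allowance for the design effect. No intracluster correlation is given.
- **Primary test** (Quantitative data analysis): "Log-rank tests with a cluster-level bootstrap will test the difference in the excess time distribution between the intervention and control groups". The same paragraph adds: "The cluster sizes are likely to be" 3–4.

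The article does not say whether weeks are resampled within arm or from a pooled null sample. Nor does it say how the p-value is formed.

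**The concern.** A bootstrap that resamples whole clusters is a large-sample device, and the number that has to be large is the number of clusters. Here that is about 30–40 in total. Resampling 15–20 weeks within each arm tends to understate the variance of the log-rank statistic. The resampled values also centre on the observed effect, so they do not form a null distribution unless they are re-centred or the null is imposed.

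This is the trial's primary test. If it is coded in one of the common within-arm forms, a true null would be declared positive more often than the stated two-sided 5%. The rate would also depend on which form was chosen at the time of coding. Because the weeks are themselves randomised, a reference distribution that follows the design is available and is not used.

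**Working it through.** **1. The plan's own figure.** Attendance of 90% against 70% gives a hazard ratio of ln(0.1)/ln(0.3) = 1.91 under proportional hazards. Expected events are 54 + 42 = 96. Schoenfeld's formula needs 75 events for 80% power, and Freedman's needs 80. With 96 events and no design effect, power is 88.8%. It stays at or above 80% up to a design effect of about 96/75 = 1.28. With design effect 1 + (m − 1) × ICC, that is an ICC of about 0.28/3 = 0.09 at m = 4, or 0.28/2 = 0.14 at m = 3. So the claimed power reproduces for a log-rank test, and the sample size is not at issue here.

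**2. Number of clusters.** 120/4 = 30 to 120/3 = 40 site-weeks, hence 15–20 per arm at 1:1. There would be more if some weeks enrol fewer than three.

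**3. Type I error, main simulation.** No treatment effect, 80% attending by 24 months, the rest censored, weeks allocated 1:1 without site strata. There were 9,600 trials per row with 499 resamples each, and Monte Carlo error of about 0.25 points. The ICC (on a latent scale) and the share of participants with zero excess time are assumptions. Entries are the percentage rejected at two-sided 5%.

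| Weeks (size) | ICC | At zero | Plain log-rank | Within-arm, SE | Within-arm, percentile | Within-arm, centred | Within-arm, SE with t(K−2) | Null imposed (pooled) | Week permutation |
|---|---|---|---|---|---|---|---|---|---|
| 30 (4) | 0 | 0% | 4.92 | 7.24 | 6.80 | 6.17 | 6.07 | 4.92 | 4.89 |
| 30 (4) | 0.048 | 0% | 6.75 | 7.71 | 7.18 | 6.49 | 6.49 | 5.23 | 5.27 |
| 30 (4) | 0.048 | 30% | 6.65 | 7.81 | 7.26 | 6.46 | 6.54 | 5.36 | 5.29 |
| 34 (3–4) | 0.048 | 30% | 6.31 | 7.60 | 7.21 | 6.22 | 6.52 | 5.27 | 5.29 |
| 40 (3) | 0.048 | 30% | 6.21 | 7.31 | 6.95 | 6.10 | 6.51 | 5.23 | 5.09 |
| 40 (3) | 0.102 | 30% | 7.19 | 7.22 | 6.84 | 6.01 | 6.46 | 5.19 | 4.97 |
| 40 (3) | 0 | 30% | 5.52 | 7.21 | 6.93 | 5.98 | 6.36 | 5.36 | 5.29 |
| 60 (1–3) | 0.048 | 30% | 5.75 | 6.71 | 6.40 | 5.65 | 6.10 | 5.03 | 5.03 |

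At 30–40 weeks, every within-arm form lies between 6.0% and 7.8%. Relative to 5%, that is 6.0/5 = 1.20 to 7.8/5 = 1.56, or 20–56% more false positives. The null-imposed bootstrap and the permutation test are practically the same.

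**4. With site strata.** A smaller simulation (32 and 38 weeks, ICC 0 and 0.05, 2,000 trials each, Monte Carlo error about 0.5 points) gave 5.8–8.3% for within-arm forms, 4.8–5.8% with the null imposed, and 4.7–5.8% for permutation within site. In another set (30–34 weeks, two sites, ICC 0–0.10, 3,000 trials each), resampling within arm and site gave 8.2–8.3%, against 4.5–5.1% for permutation within site.

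**5. Power.** In that last set, permutation had about 67–69% power and the bootstrap 74–76%. Against a plain log-rank test at ICC 0, where both hold their level, permutation lost about 3 points. These absolute powers depend on the assumed shape of the excess-time distribution; only the differences matter here.

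**The case against.** The strongest objection is that the article names no bootstrap variant. A bootstrap used to test a difference can fairly be read as resampling under the null, and that form is near nominal. The resampling algorithm is also the kind of detail that a condensed article leaves to the full protocol or analysis plan, and the article does promise that every analysis will account for the clustering. This stands in part. A reader might infer that the primary test as written runs at 7–8%. The document does not support that: the figure belongs to two within-arm forms (SE and percentile), while centred and t-based forms ran at about 6–6.5%. Nor is the article's silence on the algorithm a fault in itself.

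A reader might also infer that the bootstrap is worse than making no correction. That holds for within-arm forms when the ICC is near zero. At an ICC of 0.10 the plain log-rank test itself ran at 7.2%, about the same as the within-arm SE form (7.2%) and above the percentile (6.8%) and centred (6.0%) forms. The article gives no ICC, so the general claim fails.

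It is also fair to say that 30 clusters is the lower limit and that inflation eases with more. At 60 smaller weeks, the SE and percentile forms still gave 6.4–6.7%. Finally, permutation is less simple if the ratio of weeks changes midway, and the simulations covered only balanced allocation.

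What remains is that the article does fix a method. That method is safe in one form and runs above its level in the other common forms at this number of clusters. A concrete alternative held its level in every scenario tried.

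**Conclusion.** The point holds as a risk in a stated method, not as a demonstrated error. With about 30–40 randomised weeks, a log-rank test with a cluster-level bootstrap does not reliably hold the two-sided 5% level. Common within-arm forms run at about 6–8%. A null-imposed bootstrap or a permutation of week labels runs at about 5%.

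The cluster count follows from the article. The ICC (0–0.10), the share at zero excess time, the 80% attendance and the spread of cluster sizes are assumptions. Every within-arm form stayed above the null-imposed bootstrap and the permutation test across the ranges tried in the main simulation. The inflation is modest, but it affects the primary test and is cheap to remove. It has no bearing on the plan's power claim, which reproduces.

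**What to change.** In Quantitative data analysis, replace the bootstrap test with a sentence such as: *The p-value of the log-rank statistic will be obtained by re-randomising the intervention and usual-care labels over the enrolled site-weeks, within site, following the allocation scheme actually used, including any midway change of ratio (at least 9,999 re-randomisations).* If the ratio is changed, the rule and date should be recorded so that the re-randomisation can follow them.

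The minimum alternative keeps the planned method and adds one clause: the cluster bootstrap resamples weeks under the null of no difference between groups.

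If a cluster-bootstrap confidence interval for the difference in attendance is kept, so that the result can be read against the 20-point minimum important difference, it should be described as approximate with this number of clusters. A t cut-off does not fully repair it: for the log-rank statistic, the t-based form still ran at about 6–6.5%. The interval and the p-value may therefore occasionally disagree.

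The cost is one sentence, a few lines of code and several points of apparent power (about 67–69% against 74–76% in one set of simulations). Most of that loss is the inflated error rate being given up; against a valid plain log-rank test at ICC 0 it was about 3 points. The choice should be settled before the data are analysed.
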